## 11.2 Sample size estimates

### 11.2.1 Individual-randomised trial

A sample of 175 children with newly diagnosed HIV per arm provides 80% power to detect a 45% reduction in proportion of children who miss ≥2 routine appointments in the follow up period in the intervention arm relative to the standard of care arm, given the most likely scenario of 30% missing in the control arm 4, 86, and allow 10% loss to follow-up, assuming a baseline HIV prevalence of 1.8%. The study also has 83% power to detect a 40% difference in proportions who miss ≥2 appointments, assuming that rates in the unexposed arm is 40%.

Studies have shown virological failure rates of 30-70% in older children. 1, 87-88 Assuming that at least 70% of the 175 children per arm with newly diagnosed HIV start ART, we expect 123 children per arm to be on ART. If the treatment failure/death rate among controls is 50%, the study will have 87% power to detect a 40% reduction in this rate. Given that our retention rate into the trial is better than expected, 350 participants will therefore provide adequate power to detect the difference in retention in care between the trial arms, even with the lower sample size.

### 11.2.2 Post-PITC Prevalence Survey Sample Size Estimates

We propose to survey children aged 8-17 years from approximately all households in 90 randomly selected CEAs to investigate the prevalence of undiagnosed HIV infection. Assuming an HIV prevalence of 3% among older children and a refusal rate of 25%, a sample size of 6,500 for the cross-sectional prevalence survey will include approximately 118 HIV infected individuals. We anticipate that the prevalence of undiagnosed HIV to drop by >50% as a result of optimal PITC implementation at PHCs. This should provide a 95% CI of around 40%-60% around a prevalence of undiagnosed HIV of 50% (i.e. precision of 10%),

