**Figure 2.1 Probability of survival to different ages following mother-to-child transmission of HIV infection**

**
[figure not shown]
**

The combination of the high regional adult HIV prevalence rates during the 1990s, the lack of interventions to prevent MTCT (PMTCT) at that time, and the previously unexpectedly high likelihood of survival has led to a much bigger epidemic of “slow progressors” in the region than was anticipated. Consequences of the under-estimation of this phase of the HIV epidemic include:

- delayed diagnosis until presentation with unequivocal signs of advanced HIV with 75% of older HIV-infected children estimated to be living with HIV undiagnosed7, 13-14
- lack of development of appropriate health information and services for providing HIV care and advice on HIV prevention and sexual health for vertically-infected children as they reach adolescence
- a dearth of epidemiological studies, leading to a lack of understanding of the major causes of morbidity and mortality in older HIV-infected long-term survivors

Regionally, efforts to improve the implementation of PMTCT and the declining adult HIV epidemic will eventually lead to declines in the numbers of vertically-infected older children, but because of the intrinsic time-lag between infant exposure and reaching older childhood, long-term survivors can be expected to grow in numbers for at least a decade.12 Moreover, PMTCT coverage is incomplete (averaging 50% in the region), so that MTCT still occurs.15-16

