## 3.3 Study Design

The study will be conducted in the main PHCs of six suburbs in Southwest Harare. Each participating PHC will offer PITC routinely to 6-15 years olds over a two year period, a well as decentralised HIV care including ART initiation. Thus, children who test HIV-positive through PITC will be offered HIV care at the same PHC. At the end of two years of implementation of PITC, an anonymised HIV prevalence survey of 8-17 years olds from randomly selected dwellings in the suburbs served by the study PHCs will be conducted. The prevalence of *undiagnosed* HIV infection in the community following two years of PITC will provide an indication of the effectiveness of primary-care based routine HIV testing in providing high enough coverage of HIV diagnosis in this age-group (>80% of children diagnosed). The survey will also provide data on overall HIV prevalence by age in the considered age-group.

Children who test HIV-positive through PITC at the PHCs and reside in the study suburb where the clinic is located will be recruited into a trial of a VLW-delivered intervention to support to households of HIV-infected children aged 6-15 years. Stratified sampling will be used with randomisation of participants within clinics (1:1) to either a) primary care based HIV care or b) primary care-based HIV care plus treatment support provided by VLWs.

The intervention will be delivered over an eighteen month period, with formative work carried out to inform the design of the intervention. This will consist of qualitative interviews with care-givers of HIV-positive children attending for HIV care and health care providers (nurses, doctors, counsellors and pharmacists) at Harare Central Hospital as well as Community-based Organizations to understand the needs of households with HIV-infected children.

Children testing HIV positive at the PHCs including those recruited into the trial, will be recruited into a clinical cohort study. Data from routine clinic visit (including height, weight, clinical symptoms, incident clinical events and adherence) will be collected. In addition, detailed growth monitoring, lung function testing and a psychosocial assessment (i.e. schooling, guardianship, and disclosure) will be carried out at pre-defined intervals. The HIV care cohort will also provide a platform for immunological studies of slow-progression of HIV infection.

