***Source: MOHCW 2011 ART Update***

A total of 463,361 clients were on ART in Zimbabwe by end 2011, out of the 593,000 in need of ART, with a 35% increase in coverage from 2010 to 2011. In terms of national coverage, Zimbabwe is now at 78.1% of those who urgently require ART. The patient survival rate for 2011 was 78% and 69% for 12 months and 24 months respectively.

In 2010 Harare City Health Clinics registered approximately 2,000 new HIV patients aged between 5-14years and 45% of them were from the South-Western High Density Suburbs. (HARARE CITY HEALTH Annual Report 2010)

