**Table 4.3 Data on ART coverage 2011 (National ART programme)**

|  | **ZIMBABWE** | | **HARARE only** | | **STUDY SUBURBS only** | |
| --- | --- | --- | --- | --- | --- | --- |
|  | Children (<15years) | Adults | Children (<15years) | Adults | Children (<15years) | Adults |
| **Eligible for ART** | 2,006 | 19,934 | 96 | 1,750 | 11 | 167 |
| **Ever Initiated** | 44,877 | 477,706 | 8,963 | 97,525 | 1,821 | 9,859 |
| **Transferred Out** | 80 | 1,644 | 7 | 945 | 5 | 27 |
| **Transferred In** | 168 | 1,366 | 9 | 530 | 1 | 44 |
| **Currently On 1st Line ART** | 40,273 | 415,991 | 8,793 | 75,028 | 1,821 | 3,155 |
| **Currently On 2nd Line ART** | 332 | 6,765 | 150 | 4,199 | 62 | 99 |
| **Lost** | 247 | 870 | 61 | 136 | 0 | 14 |
| **Deceased** | 52 | 564 | 5 | 39 | 0 | 4 |

First and second-line treatment options and fixed-dose combinations (FDCs) with scored tablets are available for children. National ART Guidelines criteria (from May 2010) for starting ART in children are summarised below:

1. Paediatric WHO Clinical Stage 3 or 4 disease, irrespective of CD4 count or CD4%
2. Immunological criteria:

| **Immunological marker** | **Age-specific criteria for initiating ART** | | |
| --- | --- | --- | --- |
| **Infant ≤24 months** | **>24-60 months** | **≥5 years** |
| CD4 % | Treat all irrespective of CD4 count/ CD4% | <25% | N/A |
| CD4 count | <750cells/µl | <350cells/µl (as for adults) |

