## 8.3 Collection of data and biological samples

The selected households will be visited and anonymised HIV testing will carried out on all children resident in the households, with guardian consent and participant assent.

An oral mucosal transudate (OMT) test will be collected from all participants to test for HIV antibodies. Participants will also be asked to provide a urine sample or dried blood spot (DBS) sample to test for antiretroviral drug concentration. This will identify those individuals who may under-report their HIV status.

Each household will be allocated an anonymous identification number and one form will be completed per household with provision for more than one child per household with separate HIV testing numbers identification numbers which are linked to the household per child. A questionnaire will be administered for each household whereby information on the following will be collected:-

- Demographics information on the household:
- The numbers and ages of all children of the household
- Socioeconomic variables, including difficulties in providing food, or in finding money to go to clinic if anyone in the household gets sick
- Demographic information on each child who participates:
- Age
- Sex
- Orphanhood status
- Grade in school (or not attending school and reason)
- Absenteeism from school due to illness
- History of HIV testing (including date of, place of and reason for test) and whether accessing HIV care/on ART

Risk factors for HIV infection at household level will be identified. If consent is declined or there is no guardian available in an eligible household to provide consent to participate, demographic information about the household will be requested from a key informant. This information will be used to define likely HIV status of children through imputation.

Undiagnosed and untreated HIV infection will be defined through self-reported past HIV-testing episodes, and self-reported chronic care medication (specifically, any ART, cotrimoxazole and IPT) being received at the time of interview. Clinical patient held records and any documentation of previous HIV test will be used to confirm the information given.

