For this project, it will not be possible to conduct an HIV prevalence survey prior to implementing PHC-based PITC, to investigate the burden of undiagnosed HIV. However, based on projections of HIV prevalence and the age distribution of children in HIV care in Zimbabwe, it is estimated that 80% of older children living with vertically-acquired HIV are currently undiagnosed.8, 12, 14

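### One post-PITC survey with no baseline, no comparison area and no split of diagnoses by source cannot be read as PITC's effect on undiagnosed HIV

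*Protocol*

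**What the plan says.** Aim 2 (section 1.2) is the effectiveness of facility-based testing in reducing undiagnosed infection among children aged 6–15. Section 3.3 says that the post-PITC prevalence of undiagnosed HIV "will provide an indication of the effectiveness of primary-care based routine HIV testing", with more than 80% of children diagnosed as the mark of sufficient coverage. Section 11.2.2 goes further: "We anticipate that the prevalence of undiagnosed HIV to drop by >50% as a result of optimal PITC implementation at PHCs".

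Section 11.1 states that "it will not be possible to conduct an HIV prevalence survey prior to implementing PHC-based PITC" and supplies an assumption instead: "it is estimated that 80% of older children living with vertically-acquired HIV are currently undiagnosed". Section 2.1 gives a slightly different figure, "with 75% of older HIV-infected children estimated to be living with HIV undiagnosed". No comparison area is described.

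The outcome in section 3.4.1 is the post-PITC prevalence of undiagnosed infection. The tally in section 9.2.3 divides HIV-positive survey children into those known to be positive before the survey and those previously undiagnosed. Section 8.3 nevertheless collects "History of HIV testing (including date of, place of and reason for test", checked against patient-held records.

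Two sets of care data bear on the starting level and the background. Table 4.3 lists 1,821 children under 15 in the study suburbs as ever started on ART. Section 4.4 reports that in 2010 the city clinics "registered approximately 2,000 new HIV patients aged between 5-14years and 45% of them were from the South-Western High Density Suburbs".

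**The concern.** A single survey estimates how many infected children are diagnosed at that moment, from whatever source. It does not show how many were diagnosed because of PITC. Under the two-way tally, a child diagnosed at a hospital years before PITC, or at another service during it, sits in the same cell as a child found by PITC at a study clinic. If the true starting level was below 80%, or if diagnosis outside PITC continued at a fair rate, the result will look more favourable to PITC than it should.

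The component is meant to inform whether testing at primary care clinics is enough or community-level testing is needed. The likely direction of error favours the conclusion that clinic-based PITC is enough.

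**Working it through.** **1. The plan's own figures.** Inputs from section 11.2.2: 6,500 children, 25% refusal, 3% prevalence.

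- Yield: 6,500 × 0.75 × 0.03 = 146. The stated 118 does not follow from these inputs.
- Precision: 0.5 ± 1.96 × √(0.25/n) gives 41–59% for n = 118 and 42–58% for n = 146, so the stated interval of about 40–60% is reproduced.
- A fall of more than half from 80% means a result below 40%. The 50% around which precision is stated is a relative fall of 1 − 50/80 = 37.5%.

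**2. The starting level.** The expected infected children in Table 5.1 are 375 + 648 + 494 + 790 + 479 + 436 + 318 = 3,540. If 80% were undiagnosed, 0.20 × 3,540 = 708 would be diagnosed. Table 4.3 has 1,821 children under 15 ever on ART. The 80% can then hold only if no more than 708/1,821 = 39% of them are in the age band and almost no child is diagnosed but untreated.

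The ceiling on the undiagnosed share is 1 − (1,821 × share in age band)/expected infected. The share in band is not given, so 50–100% is an assumption. Section 4.1 gives 194,885 children aged 6–15, and section 4.2 gives 120,182 under 16. The average prevalence in Table 4.1 is 2.53%.

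| Expected infected | All in band | Half in band |
| --- | --- | --- |
| 3,540 (Table 5.1) | 49% | 74% |
| 194,885 × 2.53% = 4,931 | 63% | 82% |
| 120,182 × 2.53% = 3,041 | 40% | 70% |

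Diagnosed children not yet on ART would lower every cell. Only the 4,931 row with half in band is compatible with 80%.

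**3. Diagnosis outside PITC.** New registrations are 0.45 × 2,000 = 900 a year for all the South-Western suburbs. The protocol takes in six (section 4.1) or seven (section 5.1) of ten suburbs, so prorating gives 540–630 a year. Starting from 80% of 3,540 = 2,832 undiagnosed, with two years at each rate and no PITC:

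| New diagnoses a year | Undiagnosed after two years | Relative fall |
| --- | --- | --- |
| 630 | (2,832 − 1,260)/3,540 = 44% | 45% |
| 540 | (2,832 − 1,080)/3,540 = 49.5% | 38% |
| 315 (half of 630) | (2,832 − 630)/3,540 = 62% | 22% |
| 900 (not prorated) | (2,832 − 1,800)/3,540 = 29% | 64% |

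With 4,931 infected, the prorated rates of 630 and 540 a year leave 54% and 58%. All of this ignores deaths, ageing in and out, and transfers between clinics. It also assumes that the 2010 rate continued.

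**4. What a split by source would leave.** The denominator becomes children undiagnosed when PITC began. If that is 50–80% of the 118–146 positives, it runs from 0.5 × 118 = 59 to 0.8 × 146 = 117. The 95% half-width at a proportion of 50% is then 1.96 × √(0.25/59) = 13 points down to 1.96 × √(0.25/117) = 9 points.

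**The case against.** The strongest reply is that the protocol plans no before-and-after comparison. The listed outcome is a post-PITC prevalence and the criterion, more than 80% diagnosed, is absolute. The result is called only an indication, and the 80% undiagnosed figure is used for planning. A reader might infer that the trial will measure a fall from 80% and credit all of it to PITC. No analysis in the document does that, and the coverage question can be answered without a baseline. This part of the reply stands. It does not rescue aim 2 or section 11.2.2, which word the result as a reduction caused by PITC.

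A reader might also infer that the care data contradict the 80%. They do not settle it. Table 4.3 covers all children under 15, including those under 6. It is also inconsistent with itself: 1,821 on first-line plus 62 on second-line ART exceeds the 1,821 ever initiated. The population figures differ between sections, and one reasonable combination allows about 82% undiagnosed. The 2010 registrations may include transfers, since section 4.4 describes older children moving to primary care after starting ART.

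PITC yield is counted directly in section 9.2.1, and tabulating diagnoses by source could be left to an analysis plan. But clinic yield has no community denominator, and sections 3.4.1 and 9.2.3 do fix the survey outcome and tally without the split.

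Finally, a split by source gives no counterfactual. Section 4.3 says that testing on symptoms or request already takes place at health facilities, so some study-clinic diagnoses would have been made anyway. That is right, and limits what the fix can claim.

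**Conclusion.** The point holds as one of attribution. With no baseline, no comparison area and a two-way tally, the survey can estimate all-source coverage but cannot support a reduction as PITC's doing.

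The size is uncertain. On the Table 5.1 denominator, the starting level was at most 49–74% undiagnosed if 50–100% of the treated children are in the age band. With 4,931 infected and half in band, it could be about 82%. Prorated background registration could by itself take 80% to about 44–50%, or to 62% if only half of 630 a year were new diagnoses. Background diagnosis was therefore not negligible and could account for a substantial part of the anticipated fall.

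A reader might go further and infer that the mark of more than 80% diagnosed would be met without PITC. Starting from 80%, the scenarios on the Table 5.1 denominator leave 29–62% undiagnosed, well short of the below-20% that it requires. Meeting it would take a much lower starting level and high background diagnosis together, and the documents do not establish both.

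**What to change.** In sections 3.4.1, 9.2.3 and 11.2.2, use the date and place of test from section 8.3 to put each HIV-positive survey child into one of four groups: diagnosed before PITC began; diagnosed at a study clinic during PITC; diagnosed elsewhere during PITC; undiagnosed.

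- Report the second group as a share of the last three, that is, of all who were undiagnosed when PITC began.
- Report the reconstructed starting level in place of the assumed 80%.
- Keep more than 80% diagnosed as a coverage measure from all sources, and say so in section 3.3.
- Delete the causal phrase in section 11.2.2 and align aim 2 with what the survey can show.

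The cost is wording and tabulation, since no new data are needed. The limits should be stated. Dates and places rest partly on recall. A child recognised as diagnosed only through the antiretroviral drug test will have neither, and needs a sensitivity analysis. Only surviving residents are counted. The denominator falls to about 59–117 children (±13 to ±9 points). Some study-clinic diagnoses would have happened without PITC, so the share describes PITC's contribution and is not a causal effect.

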**POST-PITC HIV PREVALENCE SURVEY**

HIV prevalence survey after 2 years of PITC in 6000 children (aged 8-17 years)

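### The post-PITC survey's expected 118 HIV-infected children does not follow from its stated inputs (146, or 135 at the other stated survey size), and precision is given only at 50% undiagnosed, not at the 20% benchmark

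*Protocol*

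**What the plan says.** Protocol section 11.2.2 sets out the survey's inputs: "Assuming an HIV prevalence of 3% among older children and a refusal rate of 25" per cent. From these it states that "a sample size of 6,500 for the cross-sectional prevalence survey will include approximately 118 HIV infected individuals". It then gives its expectation, "We anticipate that the prevalence of undiagnosed HIV to drop by >50" per cent, and its precision: "This should provide a 95% CI of around 40%-60% around a prevalence of undiagnosed HIV of 50" per cent, described as a precision of 10%.

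Three other places bear on this:

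- Figure 1.1 gives another survey size: "HIV prevalence survey after 2 years of PITC in 6000 children".
- Section 11.1 gives the starting level: "it is estimated that 80% of older children living with vertically-acquired HIV are currently undiagnosed". The same section says that no survey can be done before PITC starts. Section 2.1 puts the starting level at 75%.
- Section 3.3 says what the survey is to indicate, namely whether clinic-based testing gives "high enough coverage of HIV diagnosis in this age-group (>80% of children diagnosed").

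**The concern.** The number of infected children found is the denominator of the survey's main estimate, the share of infected children who are still undiagnosed. If that number does not follow from the inputs printed beside it, a reader cannot tell which input was meant or how precise the survey is expected to be. Two survey sizes add to the doubt.

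The reference value is a second problem. A fall of more than half from 80% leaves less than 40% undiagnosed, and more than 80% diagnosed leaves less than 20%. Precision is quoted at 50%, which matches neither. A reader who wants to know how well the survey will measure coverage near its own benchmark does not find that figure.

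**Working it through.** **Inputs.** Survey size 6,500 (section 11.2.2) or 6,000 (Figure 1.1); prevalence 3%, refusal 25% and 118 expected infected (section 11.2.2); undiagnosed before PITC 80% (section 11.1) or 75% (section 2.1); benchmark above 80% diagnosed (section 3.3).

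**1. The plan's own interval.** Half-width = 1.96 x sqrt(p(1-p)/n). With n = 118 and p = 0.50 this is ±9.0 points, or 41.0% to 59.0%. The exact (Clopper-Pearson) interval is 40.7% to 59.3%. Both fit the stated 40%-60%, so the interval is correct given 118.

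**2. The count of 118.** Expected infected = size x (1 - refusal) x prevalence.

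| Reading | 6,500 | 6,000 |
|---|---|---|
| 25% refuse (x 0.75) | 146 | 135 |
| Size inflated for refusal (/ 1.25) | 156 | 144 |
| Size already net of refusal | 195 | 180 |

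No reading gives 118. To reach it, one input would have to change:

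- prevalence to 118 / (6,500 x 0.75) = 2.4%;
- refusal to 1 - 118/195 = 39%;
- survey size to 118 / (0.03 x 0.75) = about 5,244.

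Two other products come close. The 1.8% prevalence used in section 11.2.1 gives 6,500 x 0.018 = 117 with no refusal, and 80% of 146 is also 117. Either could be the origin, but the protocol does not say.

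**3. The values the plan points to.** Expected: 80% x 0.5 = 40%, so under 40% (75% x 0.5 = 37.5% from the section 2.1 figure). Benchmark: 100% - 80% = 20%, so under 20%.

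**4. Precision at those values**, same formula, simple random sampling:

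| Undiagnosed | n = 118 | n = 135 | n = 146 |
|---|---|---|---|
| 50% | ±9.0 | ±8.4 | ±8.1 |
| 40% | ±8.8 | ±8.3 | ±7.9 |
| 20% | ±7.2 | ±6.7 | ±6.5 |

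The two survey sizes differ by 8.4 - 8.1 = 0.3 points at 50%.

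**5. Clustering.** Sections 8.1 and 8.2 sample whole census enumeration areas and every eligible child in a household, so these half-widths are too narrow if infection or diagnosis clusters. The stated ±10 points at 50% needs 1.96² x 0.25 / 0.10² = about 96 infected children under simple random sampling. It therefore leaves room for a design effect of 118/96 = 1.23, 135/96 = 1.41 or 146/96 = 1.52. The section states no design effect.

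**The case against.** The best defence is that nothing here harms the survey. A proportion's interval is widest at 50%, so quoting precision there is a conservative convention, and the survey is more precise at 40% or 20% than the protocol claims. The error in the count also errs on the safe side, since 146 or 135 infected children give a narrower interval than 118. Recruitment is defined by area (all eligible households in 90 enumeration areas), so the number of children is an expected yield and not a quota. All of this stands.

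A reader might go further and infer that one result could support opposite conclusions: 30% undiagnosed would be a fall of more than half from 80% yet would miss the benchmark. The documents do not support that. Only the figure of more than 80% diagnosed is worded as a measure of effectiveness. The fall is introduced as something anticipated, and a drop from 80% to below 20% satisfies both statements. A result of 30% would exceed an expectation and miss a benchmark, which is one verdict.

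A reader might also test the survey by asking whether its upper 95% limit would fall below 20%. The protocol sets no such rule. It plans an estimate, and a formal rule may properly sit in an analysis plan that is not shown.

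What the defence leaves untouched is that the count is wrong on its own inputs, that two survey sizes are printed, and that no precision is given at the benchmark.

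**Conclusion.** The point holds as a correction to the sample size section. The expected number of infected children should be 146 for 6,500 children or 135 for 6,000, unless a prevalence or refusal rate other than the printed one was intended. The stated 118 is about 19% below 146 (28/146) and about 13% below 135 (17/135).

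Quoting precision only at 50% is an omission of relevance, not an undersized survey. At the 20% benchmark the half-width is about ±6.5 points with 146 or ±6.7 with 135. Neither the reference value nor the choice between the two survey sizes can reverse a conclusion.

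These figures take 25% refusal as a loss from the number approached and assume simple random sampling. The actual design will widen the intervals by an amount that the protocol gives no basis to estimate.

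**What to change.** In section 11.2.2 and Figure 1.1:

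1. State one survey size, and say whether it counts children approached or children tested.
2. Give the infected number that follows (146 for 6,500, or 135 for 6,000, if the size counts children approached), or restate the prevalence or refusal assumption that produces 118.
3. Give expected precision at 20% undiagnosed as well as at 50%: about ±6.5 and ±8.1 points with 146, or ±6.7 and ±8.4 with 135. Say that these assume simple random sampling and that sampling whole enumeration areas and all children in a household will widen them.
4. State that more than 80% diagnosed is the benchmark, and that the fall of more than half is a planning expectation, because no pre-PITC survey exists to measure it against.

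The cost is wording only. Survey procedures and the number of enumeration areas need not change.
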